#### Description of the intervention for patients included in the parallel cohort

Patients with a normal G8 score will be included in the parallel cohort and treated according to the institution’s standard management process.

### Evaluation criteria

Although OS is a usual endpoint to assess treatment efficacy in RCTs, it may not be sufficient to assess the treatment benefit in an elderly population. The effect on HRQoL should also be considered, since it may be as important as (and sometimes more than) duration of life for this population [24, 25]. Efficacy will be assessed using a co-primary endpoint encompassing OS and three targeted HRQoL dimensions including global health status, physical functioning and emotional functioning as measured using the EORTC QLQ-C 30 questionnaire [16]. Specifically, efficacy of the “case-management intervention” will be considered superior to that of “usual care” at one year, if there is a significant clinical improvement in OS without a significant deterioration in at least one of the targeted HRQoL dimensions, or if there is a significant clinical improvement in at least one of the targeted HRQoL dimension without a significant difference in OS.

OS is defined as the delay between the date of randomization and the date of death. If the absolute difference in OS at one year is at least 10% greater, then we will consider it as a significant improvement in the OS. For HRQoL, the three targeted dimensions will be assessed using the EORTC QLQ-C 30 questionnaire [16]. Dimensions will be scored according to the EORTC manual [26]. Each dimension will be scored ranging from 0 to 100 and a difference of 10 points or greater will be considered to be clinically significant [27]. If there is a major improvement in at least one of the three scales, without deterioration of the other two, then we will consider as a significant improvement in HRQoL. Secondary endpoints include PFS defined as the delay between the date of randomization and the date of progression or death whichever occurs first. Progression, as well as objective response, will be defined as per the RECIST criteria for solid tumors [28] or the Cheson criteria for lymphomas [29]. HRQoL dimensions other than those targeted for the primary efficacy endpoints will similarly be assessed based on the EORTC scoring manual, and the EORTC ELD-14 module will be assessed following published guidelines [30]. For each of the HRQoL dimensions, time until definitive deterioration (TUDD) will be investigated and defined based on a recent publication [31]. Toxicities will be graded according to the NCI-CTC v4.3 classification. For geriatric questionnaires (G8, ADL, IADL, MNA, MMSE, GDS-15, CIRS-G, TUG), cut-off scores used to define abnormal scores are those reported in the corresponding literature and summarized in Soubeyran et al. [3].

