## Methods/Design

### Objectives

#### Primary objective

The primary objective of the trial is to compare the efficacy of two treatment strategies “usual care” and “Case-management intervention” in elderly cancer patients considered in need of a geriatric assessment (G8 score ≤ 14). Treatment strategies are defined as follows:“Usual care”: Patients are treated according to ongoing standards in oncology.“Case-management intervention”: Patients are treated according to ongoing standards in oncology as in the “Usual care” arm. In addition, patients receive geriatric assessments and interventions coordinated by a geriatrician and a trained nurse, and tailored for the patient.

The intervention content for each arm has been precisely defined by a panel of experts in geriatric oncology. Efficacy will be assessed using a co-primary endpoint encompassing OS and three targeted HRQoL dimensions (global health status, physical functioning and emotional functioning as measured using the European Organization for Research and Treatment of Cancer, EORTC, QLQ-C 30 questionnaire [16]). Specifically, efficacy of the “Case- management intervention” will be considered superior to that of “Usual care” if, at one year, compared to usual care, improvement is observed for OS or at least one of the targeted HRQoL dimensions. We provide additional details of the primary endpoint in evaluation criteria and sample size calculation sections.

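### The superiority rule is stated inconsistently in Primary objective and Evaluation criteria, and as worded it can grant superiority when survival is unchanged but withhold it when survival is better

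*Protocol article*

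**What the plan says.** All places are in the protocol article.

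- **Primary objective.** Superior if, at one year, "improvement is observed for OS or at least one of the targeted HRQoL dimensions". No safeguard is attached. The section then adds: "We provide additional details of the primary endpoint in evaluation criteria and sample size calculation sections".
- **Evaluation criteria, first paragraph.** There are two routes. The OS route: "if there is a significant clinical improvement in OS without a significant deterioration in at least one of the targeted HRQoL dimensions". The HRQoL route: "if there is a significant clinical improvement in at least one of the targeted HRQoL dimension without a significant difference in OS".
- **Evaluation criteria, second paragraph.** This says when each component counts as improved. For OS: "If the absolute difference in OS at one year is at least 10% greater". For HRQoL: "If there is a major improvement in at least one of the three scales, without deterioration of the other two". For a single scale, "a difference of 10 points or greater will be considered to be clinically significant".
- **Sample size and Statistical analyses.** The alternatives are improvement in OS or improvement in HRQoL. They are tested by log-rank at 2% and three t-tests at 1% each. Neither section has a deterioration condition or a 10% OS criterion for success.

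**The concern.** These statements govern the trial's primary conclusion and cannot all be applied to the same data. Three features cause the trouble.

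1. The HRQoL route is closed by any significant OS difference, including one in favour of case management.
2. That route puts no condition on the other two scales, whereas the following paragraph does.
3. The phrase "without a significant deterioration in at least one of the targeted HRQoL dimensions" can mean that no scale is worse, or only that not all three are worse.

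Unless one rule is fixed beforehand, the verdict may depend on which sentence is applied once the results are known. It is also unclear whether the 10% and 10-point values are planning assumptions or hurdles that the observed estimates must clear, and this bears directly on the stated power.

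**Working it through.** **Reproducing the plan's figures.** Inputs from Sample size: one-year OS 50% against 60%, two-sided 2%, power 85%, 548 per group, SD 20.

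- HR = ln 0.6 / ln 0.5 = 0.737.
- Events = 4 × (2.326 + 1.036)² / (ln 0.737)² = 486, as stated.
- Power for a 10-point HRQoL difference at 1% exceeds 99.9%, consistent with the stated figure of more than 90%.
- Alpha: 2% + 3 × 1% = 5%.

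The design figures therefore stand for the plain either-or rule.

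**Same data under each statement** (deterioration on any scale taken to block the OS route):

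| Result | Primary objective | Evaluation criteria, two routes | Evaluation criteria, component definitions |
|---|---|---|---|
| OS better, one scale better, none worse | superior | superior (OS route) | both components improved if OS gain is at least 10% |
| OS better, one scale better, another worse | superior | not superior: the OS route fails on deterioration, the HRQoL route on the OS difference | no HRQoL improvement |
| OS unchanged, one scale better, another worse | superior | superior (HRQoL route) | no HRQoL improvement |
| OS worse, one scale better, none worse | superior | not superior | HRQoL improved |

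Rows two and three have identical HRQoL results. The two-route rule accepts the one with unchanged survival and rejects the one with better survival.

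**Size of that reversal.** Take true differences of +10 on one scale and −5 on another, with OS independent of HRQoL (an assumption; the article gives no correlation). Significance alone is used here, without the 10% and 10-point hurdles. The +10 is detected almost always. The −5 is detected with power 0.941.

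- OS null: the HRQoL route stays open unless OS differs at 2%, so about 1 − 0.02 = 98%.
- OS at HR 0.737: 0.15 (OS not significant) + 0.85 × (1 − 0.941) = 0.15 + 0.05 = 20%.

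A simulation of 400,000 draws, with correlation 0.5 assumed between scales, gave 98% and 20%. The plain either-or rule gave 100% in both cases.

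**Gap between the routes if OS improvement and OS difference are defined differently.** With 486 events the largest significant HR is exp(−2 × 2.326 / √486) = 0.81. One-year OS is then 0.5^0.81 = 57.0%, a gain of about 7 points. Suppose the 10% cut-off defines improvement and the log-rank test defines difference. A gain of about 7 to 10 points then closes both routes. Simulated at the design OS effect (548 per arm, exponential survival):

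- significant log-rank with an observed gain below 10%: about 33% to 35% across runs with follow-up censored at one year, and about 48% with three years of follow-up;
- the same with one-year censoring, also requiring an observed gain of at least 10 points on a scale whose true effect is +10: about 17%.

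**OS success if 10% is an observed hurdle.** The true gain is 10 points, so the observed gain reaches 10 in about half of trials. The simulated chance of a significant result with at least a 10% gain was 50%, against 85% for the log-rank test alone.

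**HRQoL success if 10 points is not a hurdle.** The standard error is 20 × √(2/548) = 1.21, so p < 0.01 is reached at 2.576 × 1.21 = 3.1 points.

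**The case against.** The best defence is that the text is a summary, then a rule, then definitions. The Primary objective section announces that details follow. The second paragraph of Evaluation criteria defines the terms used in the first. On that reading there is a single rule, and a trial with OS unchanged, one scale better and another worse has one answer: not superior. This part stands: a reader might infer three complete rival rules, but the component definitions are not a separate superiority rule, and the opening statement is partly a pointer. It does not remove the conflict. A promise of further detail does not turn an unconditional either-or into a conditional rule, the planned tests follow the unconditional version, and the HRQoL route still excludes an OS benefit.

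The second defence is that the gap between routes depends on using two meanings of *significant* within one rule. This is correct. With the log-rank test throughout, a significant gain meets the OS part of the first route. With the 10% cut-off throughout, a 7-point gain is not a difference and the HRQoL route stays open. A reader might infer that about a third of trials would be lost to this gap. The documents support that only under the mixed reading, and that figure does not require any HRQoL gain.

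A reader might also infer that the two-route rule alone can reject a trial in which survival and HRQoL both improve and nothing worsens. It cannot: such a trial succeeds through the OS route unless the 10% cut-off is brought in.

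**Conclusion.** The point holds: the success rule is inconsistent as written and should be reconciled, because it decides the primary conclusion. Two parts need no simulation. The statements classify a mixed HRQoL result with unchanged OS differently. The two-route rule also rewards unchanged survival over better survival when one scale improves and another deteriorates. The 98% against 20% contrast illustrates the second part; it rests on the assumed +10 and −5 effects, on independence of OS and HRQoL, and on reading the deterioration clause as any scale.

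The 7-to-10-point gap is conditional on the mixed definitions and vanishes once one definition is used. The fall in OS success from 85% to about 50% is conditional on 10% being an observed-value criterion, which is the literal reading of the Evaluation criteria text.

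A reader might infer a type I error problem. There is none: the extra conditions can only remove successes relative to the plain either-or, whose alpha sums to 5%. The stated sample size also reproduces. What suffers is power and the interpretability of the result.

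**What to change.** State one rule and use it in Primary objective, Evaluation criteria, Sample size and Statistical analyses.

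1. In the HRQoL route, replace the requirement of no significant OS difference with *OS not significantly worse*.
2. In the OS route, replace deterioration in at least one scale with *deterioration in any scale*.
3. Apply the no-deterioration condition on the other two scales to the HRQoL route, and say how deterioration is tested.
4. Use one definition of significant for OS in both routes.
5. State whether 10% and 10 points are design assumptions or observed-effect success criteria. If criteria, restate the OS power. If assumptions, acknowledge that an HRQoL difference of about 3.1 points could count as success.

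Item 5 must be decided openly, because quietly substituting p-values for the thresholds would change the endpoint. The change is to wording only and needs no new data. The cost is that the HRQoL route may become slightly harder to meet, and the stated OS power may fall.

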#### Sample size

Sample size was estimated for the randomized trial. For the null hypothesis we assumed no difference in OS and no difference in the three targeted HRQoL dimensions between the two intervention arms. Alternative hypotheses were two-fold: improvement in OS or improvement in HRQoL. The 5% two-sided type-1 error rate was therefore split between the two alternative hypotheses with 2% for OS and 1% for each of the three HRQoL dimensions. Sample size improvement for testing improvement in OS assumed the following hypotheses: 2% (two-sided) type-1 error rate, 85% power, anticipated 1-year 50% OS rate in the ‘usual care’ group [13], 60% expected 1-year 60% OS rate in the “Case-management” arm (ie anticipated hazard ratio, HR = 0.74). These hypotheses led to an estimated sample size of 1096 subjects (548 per group; 486 events) needed to detect a difference in OS (log-rank test). Sample size for testing improvement in HRQoL was based on a 3% (two-sided) type-1 error. If the intervention is effective, we expect that it will allow us to detect, at one year, a mean difference of 10 points or more for at least one of the three targeted HRQoL scores (common standard deviation of 20 points). Each of the three scales will be independently tested. Five hundred and forty eight subjects per group (as needed for OS comparison) will provide sufficient power (>90%) for independently testing the three HRQoL scales at 1% (2-group t-tests of equal means – common variance).

To anticipate for non-assessable subjects (10%), 1200 patients need to be randomized (ie with G8 score ≤ 14). Based on previous research [5] about 80% of the patients are expected to have positive G8, thus 1500 patients need to be screened for inclusion in the randomized trial.

Since 20% are expected to have normal G8 score, about 300 patients will be included in the parallel cohort. Following our previous experience with the ONCODAGE validation study [3] which included 1668 patients over 18 months, we expect that 800 patients will be screened each year, leading to an expected inclusion period of 1.5 to 2 years. To reach all endpoints, three years of follow-up are required, giving total study duration of 5 years.

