#### Statistical analyses

For the randomized trial, different analysis sets will be defined including the intent-to-treat (ITT) population (all randomized patients included and analyzed according to the allocated intervention), modified ITT population (mITT: all randomized patients with baseline HRQoL included and analyzed according to the allocated intervention) and per protocol population (PP: eligible patients and analyzed according to the intervention actually received). These three populations will be described according to the following characteristics: compliance with eligibility criteria, epidemiological characteristics, clinical and laboratory characteristics, treatment characteristics, and HRQoL. For the co-primary endpoints, the primary analysis will be conducted in the mITT population, with sensitivity analyses conducted in the PP population. OS will first be compared based on a log-rant test stratified on randomization factors (2% type 1 error rate). Additional analyses will be conducted including Cox regression modeling to provide an estimate of the effect size of the intervention, after checking for underlying model assumptions. For each targeted HRQoL dimension, a *t*-test assuming common variances will be conducted (1% type 1 error rate). Sensitivity analyses assuming a mean difference of 5 points or more for at least one of the targeted HRQoL scores will be conducted. In addition, variance analysis will be conducted for adjustment on randomization factors and additional covariates. Other endpoints will be analyzed using standard statistical techniques. PFS will be analyzed using the same methods as for OS. Censoring mechanisms for the analysis of TUDD will follow recommendations from Bonnetain et al. [28]. With regards to HRQoL data, missing data analysis will be performed to determine the missing data profile. Longitudinal models will be fitted to provide a description of the HRQoL over time and investigate effect of the intervention. For patients treated in the “Case-Management” arm, the analysis of geriatric parameters will involve summary statistics presented at various time-points as well longitudinal analysis to investigate trends over time.

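### Read literally, the success rule sets cut-offs (10% in OS, 10 points in HRQoL) equal to the planning effects, while the stated power covers only tests against zero

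*Protocol article*

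**What the plan says.** **Success rule (Evaluation criteria).** Case management is superior at one year in either of two situations. One is a significant clinical gain in OS without HRQoL deterioration. The other is such a gain in at least one targeted HRQoL scale without a significant OS difference. The section then explains its terms. For OS: "If the absolute difference in OS at one year is at least 10% greater, then we will consider it as a significant improvement". For HRQoL: "a difference of 10 points or greater will be considered to be clinically significant", followed by a sentence that counts a major improvement on one scale, with no deterioration on the other two, as a significant HRQoL improvement. The Primary objective section speaks of improvement being observed.

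**Power (Sample size).** The 5% error rate is "split between the two alternative hypotheses with 2% for OS and 1% for each of the three HRQoL dimensions". The OS inputs are "2% (two-sided) type-1 error rate, 85% power, anticipated 1-year 50% OS rate", a 60% one-year rate with case management, and "anticipated hazard ratio, HR = 0.74". They lead to "1096 subjects (548 per group; 486 events) needed to detect a difference in OS (log-rank test". For HRQoL the assumed difference is 10 points or more on at least one scale with a standard deviation of 20. The 548 per group are said to give more than 90% power for each t-test at 1%.

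**Analysis (Statistical analyses).** A stratified log-rank test at 2% and t-tests at 1% are named, with no cut-off. The section adds: "Sensitivity analyses assuming a mean difference of 5 points or more for at least one of the targeted HRQoL scores will be conducted".

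**The concern.** The same two numbers do two jobs. In the sample-size section, 10% and 10 points are the true effects the tests are sized to detect. In the evaluation criteria they read as marks the result must reach. These are different rules. An approximately symmetric, unbiased estimate of a true 10-point effect falls below 10 about half the time, so a criterion that asks the estimate to reach 10 does not have the power of a test against zero.

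At stake is the primary conclusion. An OS result that is significant at 2% but shows a difference of, say, 8 percentage points is a success under the analysis section and not an improvement under the evaluation criteria. If this stays open, the choice between the two could be made after the data are seen.

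**Working it through.** **Inputs, all from the Sample size section:** one-year OS 50% and 60%; OS alpha 2% two-sided; 548 per group; 486 events; HRQoL difference 10, SD 20, alpha 1% two-sided per scale.

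**1. The plan's own figures, tests alone.**
- HR = ln 0.6 / ln 0.5 = 0.737.
- Events = 4 × (2.326 + 1.036)² / (ln 0.737)² = 486 for 85% power. This matches the stated number.
- HRQoL: SE = 20 × √(2/548) = 1.21; power = Φ(10/1.21 − 2.576), above 99.9% per scale. This is consistent with the stated figure of more than 90%.

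**2. Where the tests become significant.**
- Log-rank: critical HR = exp(−2.326 × 2/√486) = 0.81, that is 0.5^0.81 = 57.0% against 50%, or about 7 percentage points.
- t-test: 2.576 × 1.21 = 3.1 points with 548 per arm. With an assumed 300 assessable per arm, it is 4.2 points.

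Both lie well below 10, so the cut-offs would be the binding condition.

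**3. Chance of meeting each cut-off when the planning effect is true.**
- OS: SE of the one-year difference = √(0.25/548 + 0.24/548) = 0.0299; P(observed ≥ 0.10) = 1 − Φ((0.10 − 0.10)/0.0299) = 50%.
- HRQoL: 1 − Φ((10 − 10)/1.21) = 50% per scale.
- The numerator is zero in both cases, so a larger sample does not change the result.

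**4. Simulation for OS** (10,000 trials, 548 per arm, exponential survival, everyone followed to one year):

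| Event | Share of trials |
|---|---|
| Log-rank p < 0.02 in favour of case management | 85.4% |
| Observed difference ≥ 10% | 50.2% |
| Both | 50.2% |
| Significant but below 10% (85.4 − 50.2) | 35.2% |

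**5. True effects needed to restore the stated power under the cut-offs.**
- OS, 85%: 0.10 + 1.036 × 0.0299 = 0.131, about 13.1 percentage points.
- HRQoL, 90%: 10 + 1.282 × 1.208 = about 11.5 points at 548 per arm (about 12.1 at 300 per arm).

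**6. More than one endpoint benefiting.** The article gives no correlations, so these are assumed.
- All three scales truly differ by 10: at least one HRQoL cut-off is met in 69% (correlation 0.7) to 80% (correlation 0.3) of trials.
- OS also has its planning effect, independent of HRQoL: P(at least one of four) = 1 − 0.5 × (1 − P(at least one scale)). With between-scale correlation 0.9, 1 − 0.5 × (1 − 0.61) = about 80%; with correlation 0, 1 − 0.5 × (1 − 0.875) = about 94%.
- Only one endpoint benefits: that endpoint's criterion is met about 50% of the time.

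The figures in step 6 count cut-offs met, before the no-deterioration conditions.

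**The case against.** The strongest reply is that 10% and 10 points are only the clinically relevant differences the trial is sized to detect. The sample-size section states nulls of no difference, the analysis section names plain tests, and the definitions in the evaluation criteria do not say that the cut-off applies to the estimate. On that reading 85% and more than 90% stand. This is a possible intention, but it does not remove the conflict: the OS sentence is an if-then rule placed among the success criteria and would then need rewording. Nor is this detail an article may leave to a fuller protocol, since the article states both rules.

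Several parts of the reply stand:

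- The HRQoL cut-off is less explicit than the OS one. It comes from linking the 10-point clinical-significance sentence and the unnumbered major-improvement sentence to the superiority rule.
- The 5-point sensitivity analysis supports a cut-off reading for HRQoL, because a t-test of equal means takes no assumed difference. It could also mean interpretation against a smaller relevant difference, and it says nothing about OS.
- Requiring both significance and clinical relevance is a legitimate design. Whether to drop that requirement is the sponsor's decision.

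A reader might go further and infer that the trial's real power is 50%, or that a trial working exactly as planned fails half the time. The documents do not support that. The rule is either/or, and the chance of meeting at least one cut-off is higher if several endpoints benefit. The HRQoL assumption is also 10 points or more, so 50% describes its lower boundary. Nor is the sample-size arithmetic wrong; it answers for a different rule.

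**Conclusion.** The point holds as a conflict between the success rule and the rule that was powered. Either the evaluation criteria or the stated power is wrong as written.

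If the cut-offs apply to observed differences, the per-endpoint chance of meeting them at the planning effect is about 50%, against the stated 85% for OS and more than 90% per HRQoL scale. That comparison is like for like, because the stated powers are also per endpoint. For OS the two rules give opposite answers in about 35% of trials in which the planned effect is true. The per-endpoint 50% needs only an approximately symmetric, unbiased estimate. The 35% rests on exponential survival with complete one-year follow-up, and the ranges for several endpoints rest on assumed correlations.

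**What to change.** Reconcile the Evaluation criteria with the Sample size and Statistical analyses sections before any analysis, in one of two ways.

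- **(a) The tests decide.** Define significant improvement, significant deterioration and significant difference by the stated tests, with direction: stratified log-rank two-sided p < 0.02 for OS and two-sided p < 0.01 for each HRQoL scale. Describe 10%, 10 points and 5 points as values for interpreting the estimate and its confidence interval.
- **(b) The cut-offs decide as well.** State that they apply to the observed difference and form part of the success rule. Restate power as about 50% per endpoint at the planning effect, and give the true effects needed for the stated levels (about 13.1 percentage points for 85% in OS; about 11.5 points for 90% per HRQoL scale at 548 per arm). Add the power of the either/or rule under stated assumptions, including the no-deterioration conditions.

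Both change text and not the sample size, but the choice is one of substance. Under (a), a significant effect below 10 would count as success, from about 7 percentage points in OS or 3.1 points in HRQoL at 548 per arm, with its clinical relevance judged separately. Under (b), the stated per-endpoint power falls.
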